**Methods:**

The sample will be selected at random from individuals diagnosed with PD in the city of Florianopolis (SC, Brazil). Sample size calculation was performed with the G*Power 3.1.9.2 software, with 0.447 effect size, at 5% significance level, power of 0.9, and test and sample loss of 20%. This yielded 60 individuals divided between the intervention and control groups. The questionnaires will be filled out before and after the dance intervention. The data collection for the control group will be held simultaneously to the intervention group. The classes will last for 1 hour, twice a week in the evening for 12 weeks, and all classes will be divided into warm-up, main part, and relaxation. Two-way analysis of variance with repeated measures and Sidak post-hoc comparison test will be used for a comparative analysis of the final results of the control group with the experimental group and of the within-group changes between pre- and postintervention period.

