### Statistical Analysis and Sample Size

Sample size was based on primary outcomes and calculation performed with the G*Power 3.1.9.2 software [28], assuming a moderate effect of Brazilian samba on motor signals (UPDRS III), according to Cohen [29] with 0.447 effect size. We chose a more cautious effect size because there is still no evidence of Brazilian samba in DP rehabilitation. However, due to the effects already found in similar interventions (ref=-0.62/-0.55) [30] as described in the meta-analysis by Lutzke et al, a significant effect is expected regarding to motor symptoms. We used alpha=.05 and power of 0.9, applied in two groups (experimental group and control group) analyzing the results through a two-way analysis of variance (ANOVA) with repeated measures and Sidak post-hoc comparison test for a comparative analysis into and between groups. Significance level will be set at 5%. Anticipating 25 individuals in each group, but foreseeing a sample loss of around 20% [31,32], we have chosen to include 30 individuals per group, ending with a total of 60 subjects.

After the intervention, the data will be transferred to SPSS v. 20.0. First, descriptive statistics will be performed (mean, standard deviation, and percentage). Two-way ANOVA with repeated measures and Sidak post-hoc comparison test will be used for a comparative analysis of the results of the control group with the experimental group and of the within-group changes between pre- and postintervention period. Significance level will be set at 5%.

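### The plan points the ANOVA at group results and within-group changes, and never names the group × time term as the test of the samba effect in this non-randomised comparison

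*Protocol article*

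**What the plan says.** The objective is comparative: the effects of a 12-week samba programme are to be set against a group without intervention (Abstract, Objective; Introduction). The study is called quasi-experimental in the Abstract and non-randomised under Study Type. There are two groups and two assessments, before and after the 12 weeks (Data Collection).

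The analysis is described three times.

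- Abstract, Methods: the ANOVA with Sidak post-hoc test is for a "comparative analysis of the final results of the control group with the experimental group and of the within-group changes" between the two assessments.
- Statistical Analysis and Sample Size, on the sample size: "Sidak post-hoc comparison test for a comparative analysis into and between groups".
- The same section, on the analysis: "Two-way ANOVA with repeated measures and Sidak post-hoc comparison test will be used for a comparative analysis of the results of the control group" compared with the experimental group, and of pre-to-post changes within groups. The word final does not appear here.

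None of the three names a group × time interaction, a between-group difference in change, or an adjustment for baseline.

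**The concern.** The question is whether people who dance change more than people who do not. Neither comparison that the article spells out answers this cleanly without randomisation.

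A difference in final scores is the samba effect plus whatever difference existed at the start. The direction of that difference is unknown, so it can create an apparent effect or hide a real one.

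A pre-to-post test inside one arm uses no information from the other arm. Practice, expectation or continuing physiotherapy could move both arms. A significant change among dancers beside a non-significant one among controls is then easily read as a samba effect, although it is not a test of one.

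The 5% level stated in the plan would therefore not be the error rate of the claim that readers most want to make.

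**Working it through.** **The plan's own sample size.** Inputs from Statistical Analysis and Sample Size: "We used alpha=.05 and power of 0.9, applied in two groups"; "according to Cohen [29] with 0.447 effect size"; "Anticipating 25 individuals in each group". The section does not say whether 0.447 is Cohen's f or d, which ANOVA term it refers to, or what pre-post correlation ρ was used, so the 25 per group cannot be reproduced uniquely. Reading 0.447 as f, with N in total and two measurements:

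- Between-groups term: λ = f²·N·2/(1+ρ). At N = 50 and ρ = 0.8, λ = 0.1998 × 50 × 2/1.8 = 11.1 and power is 0.904. The required N is 50 at ρ of 0.75 to 0.8, 48 at 0.7 and 42 at 0.5.
- Group × time term, under G*Power's default convention: λ = f²·N·2/(1−ρ). The required N is 16 at ρ = 0.5, 12 at 0.7 and 8 at 0.8.

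So the stated size matches a between-groups term for some values of ρ and does not match the interaction under this convention. This fits the wording of the plan but does not prove which term was intended.

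**Final-score comparison with no samba effect.** Inputs: 25 per group (from the plan); a baseline gap δ in SD units that persists to the end (my assumption). Two-sample t test, 48 df, noncentrality δ·√(25/2):

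- δ = 0.3: 0.3 × 3.536 = 1.06; rejection 18.0%.
- δ = 0.5: 0.5 × 3.536 = 1.77; rejection 41.0%.
- For smaller gaps, the same formula gives 6% at δ = 0.1 and 11% at δ = 0.2.

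Simulation (10,000 runs, ρ from 0.5 to 0.8) agrees: 17 to 18% and 41 to 42%.

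**Within-group tests with equal change in both arms.** Inputs: 25 per arm; the same true change dz in each arm, in SD of change (assumed). Paired t test, 24 df, noncentrality dz·√25, power p. The arms are independent, so the chance that samba is significant and control is not is p(1−p):

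- dz = 0.3: p = 0.302; 0.302 × 0.698 = 0.211.
- dz = 0.4: p = 0.484; 0.484 × 0.516 = 0.250.

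The product cannot exceed 0.25, so these values lie at or near its maximum. Outside that range it falls: 7% at dz = 0.1, 15% at dz = 0.6 and 3% at dz = 0.8.

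**Group × time in the same scenarios.** In the simulations with no effect, with or without a baseline gap (0.3 or 0.5 SD) and a shared trend (0.3 SD of the score), it rejected in about 5% of runs.

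**The opposite error.** With a true benefit of 0.447 SD and an adverse baseline gap of the same size, the final-score test rejected in about 5% of runs. Group × time rejected in 35 to 69% for ρ from 0.5 to 0.8.

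**Sidak.** For k comparisons in a family, adjusted p = 1 − (1 − p)^k. Each factor has two levels. If each simple effect is its own family, k = 1 and adjusted p = p.

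**The case against.** The strongest reply is that a two-way repeated-measures ANOVA contains the group × time term by default, and post-hoc contrasts normally follow that omnibus test. The Methods speak only of results, not final results, which is compatible with testing the interaction. An article may also leave the choice of term to the full protocol or analysis plan.

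Much of this stands. The model can answer the question, and the document states no rule for declaring efficacy. A reader might infer that samba will be declared effective whenever the dancers' p value is below 0.05 and the controls' is not; the text does not say so. Nor is a final-score comparison wrong in itself: in a randomised trial it would be a valid test of effect. Here the weakness comes from the allocation, and its size depends on a baseline gap that nobody can know yet.

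What does not stand is that this is only missing detail. The article says three times what the analysis is for, the Abstract specifies final results, and the comparison that matches the objective is absent each time.

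On Sidak, a reader might conclude that the step is useless. That holds only if each two-level simple effect forms its own family. The document does not define the family, and applied across several contrasts Sidak would adjust.

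**Conclusion.** The point holds in this form: the plan describes two uses of the ANOVA and never makes group × time the test of the samba effect, in a study where allocation gives no protection against baseline differences. At 25 per group, relying on the named comparisons could mean an error rate of about 18% (assumed gap 0.3 SD) to 41% (0.5 SD) for final scores. The misleading pattern of one arm significant and the other not would occur in about 21 to 25% of studies under an assumed equal change of 0.3 to 0.4 SD. The gap and the shared change are assumptions; with neither, the final-score test keeps its 5% level.

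Two stronger readings are not supported. One is a familywise error of 1 − 0.95⁴ = 18.5% per outcome: it assumes independence and counts a baseline contrast between groups that the plan does not name and that could not support an efficacy claim. The other is that change-score and baseline-adjusted analyses are interchangeable. With a baseline gap δ they differ by δ(1−ρ), for example 0.3 × 0.5 = 0.15 SD at ρ = 0.5 and 0.3 × 0.2 = 0.06 SD at ρ = 0.8, so one must be chosen in advance.

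**What to change.** In the Abstract (Methods) and in Statistical Analysis and Sample Size, state that:

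- the samba effect on the primary motor outcome, UPDRS III, is tested by the group × time term, that is, the between-group difference in pre-to-post change, reported with its 95% CI, and this test alone decides;
- a baseline-adjusted group difference, if wanted, is a prespecified sensitivity analysis and is not equivalent to the change-score contrast when baselines differ;
- final-score and within-group comparisons are descriptive or secondary;
- the Sidak family is defined, noting that the step adjusts nothing if each two-level simple effect is its own family.

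The same edit should say which term, effect metric and pre-post correlation the sample size refers to. The cost is a few sentences and no new data. The limit should be stated too: group × time removes a fixed baseline difference, but remains biased if the non-randomised groups would have changed differently without samba.

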## Discussion

### Principal Findings

The major inspiration for this study was to encourage the creation of new rehabilitation programs that do not emphasize doctor involvement. A further goal was to provide an environment where patients, caregivers, and teachers can interact in a friendly and relaxed manner, while stimulating and encouraging social relations, important for maintaining of the well-being of patients [21].

Dance, already used as a rehabilitation tool with other diseases [33,34], has properties that address important aspects of PD [12,13]: music stimulates affective memory and the rhythm engages different neural regions [35]. Dance replaces treatments or exercises that sometimes discourage patients. In addition, because it embraces natural movements to the human being [36], dance stimulates control and motor actions, which are of great value to individuals with PD [10-13].

The positive results already found in similar studies lead us to believe in the potential of this intervention for these individuals. The protocol’s main characteristics are based on four pillars: gradual progression, stimulation of adaptability, constant revision, and provision of a lively environment during the activities. The first two pillars mainly involve motor symptoms such as gait control and balance, while the last two pillars stimulate non-motor symptoms such as cognitive stimulation and memory, providing an enjoyable activity leading to a reduction in fatigue and depressive symptoms, in addition to stimulating social interaction.

The gradual progression of difficulty of the exercises will facilitate learning and give students the motivation to learn new steps. Introduction of new steps every 2 weeks (except when the turns are taught) is extremely important in PD because the motor skills essential to daily activities often require adaptability to changing environments and the ability to deal with unpredictable fluctuations in the disease. Therefore, expanding the motor skills repertoire must be constant [9].

Further, stimulating memory function is no less important than stimulating adaptability. The process of constantly reviewing the steps already learned will promote the exercise of cognitive abilities, instigating memory formation, and activation of neural areas that normally have a reduced activity in PD [15,37]. The basic samba steps, characterized by steps forward and back and performed rhythmically, can stimulate cortical activation, as has been observed in tango, increasing the attention and concentration, especially in regards to mobility [14].

### Conclusions

This is a unique protocol for individuals with PD, which can be an important tool to alleviate motor and non-motor symptoms. Currently, validated study protocols for this population are geared mostly to exercises for specific motor tasks [38,39], ways to run long-term monitoring and management of the patients [40,41], or even different types of dance [42]. Dance is a simple activity depending on little equipment and few financial resources, facilitating its implementation and improving the cost-benefit relationship. In addition, activities that have a cultural aspect for the population in question, and which are pleasant, enable the participants to commit long term. This can enhance patient’s compliance with therapy, which is often a problem for many rehabilitation programs [14].

While these benefits are important on the international scene, they present great value in countries similar to Brazil, which faces challenges in funding disease treatment and has limited investments for research in rehabilitation.

## Appendix

Multimedia Appendix 1 Brazilian samba protocol for 12 weeks to PD patients.

## Abbreviations

BBS: Berg Balance Scale
BDI: Beck Depression Inventory
Bpm: beats per minute
CCR: Health Sciences and Sports Centers at State University of Santa Catarina in Santa Catarina Rehabilitation Center
FSS: Fatigue Severity Scale
HY: Hoehn and Yahr
PD: Parkinson’s disease
PDQ-39: Parkinson’s Disease Questionnaire
PDSS: Parkinson’s Disease Sleep Scale
UPDRS: Unified Parkinson’s Disease Rating Scale
